### Recruitment of participants

2.11

The study will be carried out at Proctology Department in Changshu Hospital Affiliated to Nanjing University of Chinese Medicine, and the patients will be recruited from inpatients via posters in the department.

### Randomization and blinding

2.12

Patients will be randomly divided into treatment group (QZD group) and control group (PB group) according to a computer-generated randomization list after the recruitment in a 1:1 ratio, and the random number table will be sealed in a special envelope to be kept in a safe place until the study is complete. Due to the differences in appearance, taste, dosage, and administration methods between QZD and PB, a double-blinded and double-dummy design will be applied. The simulations are composed of amylum. Patients in both groups would take medications and stimulations simultaneously. The researchers, drug administrators, and patients are all unaware of the blind design, and the evaluators and the statisticians are not involved in the trial.

### Discontinue and data monitoring

2.13

The supervisor will decide for discontinuing if more than 25% of the patients quit treatment due to AEs. Demographics, assessment, and cause of drop-outs will be recorded in Case report forms (CRFs), which will be submitted to the data management committee at the end of the study. All CRFs will be stored in a locked cabinet. The data management committee is independently chaired by the Statistics Teaching and Research Office of Changshu Hospital Affiliated to Nanjing University of Chinese Medicine and declares no conflict of interest. All CRFs will be preserved for at least 5 years after publication, and the access to the original data of readers and reviewers are available from the corresponding author on reasonable requests.

### Statistical methods

2.14

Statistics will be analyzed with the SPSS 22.0 (SPSS Inc., Chicago, IL). Statistical testing is 2-sided and *P* < .05 is considered statistically significant. Efficacy outcome parameters will be analyzed on an intent to-treat basis, and the last observation carried forward rule will be applied to manage missing data. The results will be reported in descriptive statistics. According to the homogeneity, group *t* test for normally distributed data or Mann-Whitney *U* test for non-normally distributed data will be used to compare variables between groups.

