### Study design

2.1

The study is a single-center, double blinded, double doomy, randomized, controlled clinical trial. The study has been approved by the Ethics Committee of Changshu Hospital Affiliated to Nanjing University of Chinese Medicine, and the trial will be carried out in accordance with the Declaration of Helsinki. The clinical trial has been registered on open science framework on January 18, 2022 (Registration number: DOI 10.17605/OSF.IO/C8MHW). The protocol conforms to the Standard Protocol Recommendations for Interventional Trials (SPIRIT) 2013 statement,^[20]^ and the results will be reported according to the CONSORT statement extension for trials.^[21]^ The schedule of enrollment, interventions, and assessments is shown in Table 1.

**Table 1 T1:** Schedule of enrollment, intervention, and assessments.

	Enrollment	Treatment					Follow up
Time point	Week 0	Week 1	Week 2	Week 4	Week 6	Week 8	Week 16
Enrollment							
Eligibility screen	√						
Informed consent	√						
Demographics	√						
History of disease	√						
Allocation	√						
Intervention							
QZD+PB-simulation		√	√	√	√	√	
PB+QZD-simulation		√	√	√	√	√	
Assessments							
IBS-SSS		√	√	√	√	√	√
IBS-QOL	√					√	√
HAMD scale	√					√	√
Recurrence rate							√
Adverse effects				√		√	

HAMD = Hamilton depression, IBS-QOL = irritable bowel syndrome-quality of life questionnaire, IBS-SSS = irritable bowel syndrome symptom severity score, PB = pinaverium bromide, QZD = Qinghua Zhixie decoction.

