#### Primary outcome

2.7.1

Irritable bowel syndrome symptom severity score (IBS-SSS)^[22]^ is the primary outcome to record the degree and frequency of abdominal pain, abdominal distention, defecation satisfaction, and quality of life at weeks 0, 1, 2, 4, 6, 8, with 4 grades: remission (less than 75 points), mild (76–175 points), moderate (176–300 points), and severe (over 300 points).

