#### Secondary outcomes

2.7.2

(1)Quality of life: The IBS-quality of life questionnaire^[23]^ will be applied to to assess the patients’ quality of life with the following aspects: emotional state, psychological state, sleep, energy, daily activities, eating habits, social activities, major activities or work, and sex life, and a higher score reflects a lower quality of life. The questionnaire will be completed before and after treatment.(2)Psychological states: The Hamilton depression scale^[24]^ will be used to evaluate the depressive states of patients during the clinical trial, and the Hamilton Anxiety scale^[25]^ for anxiety. The questionnaires will be completed before and after treatment.(3)Recurrence rate: Patients will be followed up for another 8 weeks after the treatment, and the recurrence will be observed at week 16. If the IBS-SSS of a cured patient changes from remission to mild or a more severe state, he will be considered as recurrence.^[26]^ The recurrence rate = recurrent patients/total follow-up patients × 100%.

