### Sample size

2.10

According to our preliminary experiment, QZD and PB are expected to reduce the IBS-SSS by 115 points and 105 points, respectively. Taking α = 0.05, β = 0.2, SD = 37, 212 cases will be needed in each group. Considering a loss to follow-up of 10%, 464 cases in total will be included.

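### Recurrence at week 16: the LOCF rule in section 2.14 and the recurrence formula in section 2.7.2 do not agree on patients lost after week 8, and LOCF, if applied, can only score a lost remitter as not recurrent

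*Protocol article*

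**What the plan says.** Section 2.14 (Statistical methods) gives one rule for missing data: "Efficacy outcome parameters will be analyzed on an intent to-treat basis, and the last observation carried forward rule will be applied to manage missing data". No outcome is exempted.

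Section 2.7.2 (Secondary outcomes, item 3) sets the timing of recurrence: "Patients will be followed up for another 8 weeks after the treatment, and the recurrence will be observed at week 16". It defines the event: "If the IBS-SSS of a cured patient changes from remission to mild or a more severe state, he will be considered as recurrence". It gives the rate: "The recurrence rate = recurrent patients/total follow-up patients × 100" (as a percentage). It does not say whether the denominator is the patients who enter follow-up or those seen at week 16.

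The grades come from section 2.7.1: "remission (less than 75 points), mild (76–175 points), moderate (176–300 points), and severe (over 300 points"). Table 1 lists IBS-SSS at week 8 and week 16 with no visit between them. Section 2.10 plans for some loss: "Considering a loss to follow-up of 10%, 464 cases in total will be included".

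**The concern.** Recurrence compares two grades, one at the end of treatment and one eight weeks later. If the later grade is missing and the earlier one is carried into its place, the week-8 grade is compared with itself. The answer is then fixed before anything is known about the patient after treatment. LOCF on a continuous score is different, because there a carried value may err in either direction. Here the error has one direction: a lost relapser is counted as a lasting success.

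The formula in section 2.7.2 can be read another way, with lost patients leaving the denominator. That avoids the forced result but departs from the intent-to-treat and LOCF rule in section 2.14. With both texts in force, the analyst can choose between two rates after seeing the data. Assessing recurrence is the only purpose that section 2.9 gives for the follow-up period, so this choice decides what the trial reports on durability.

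**Working it through.** **Inputs from the protocol article.** 464 patients at 1:1 give 464/2 = 232 per arm (sections 2.2 and 2.10). Loss to follow-up is 10% (section 2.10). Tests are two-sided at 5% (section 2.14).

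**Inputs not in the document, so assumed.** Share in remission at week 8: r = 0.3 to 0.5. Relapse among remitters by week 16: q = 0.3 to 0.5. Both are the same in the two arms, so there is no true difference. Arm-specific loss is as stated in each case below. The test is a pooled two-proportion z test, which the protocol does not name. A cured patient is taken to be one in remission at week 8.

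**The plan's own figures.** The plan gives no figure for recurrence. Its sample size concerns the primary outcome: 2 × (1.96 + 0.8416)² × 37² / (115 − 105)² = 214.9, or 215 per group, close to the stated 212. Nothing here depends on it.

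**Step 1: the rule.** Recurrence = 1 if the week-8 grade is remission and the week-16 grade is mild or worse. With week 16 replaced by week 8, it is 0 for every remitter. This needs no assumption beyond LOCF being applied.

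**Step 2: formulas.** Let l be the share lost, and let l_R be the share of relapsers lost.
- LOCF, all randomised patients in the denominator: r·q·(1 − l_R).
- Followed-up denominator, loss unrelated to relapse: r·q·(1 − l)/(1 − l) = r·q.
- Followed-up denominator, only relapsers lost: r·q·(1 − l_R)/(1 − r·q·l_R) for all patients seen, or q·(1 − l_R)/(1 − q·l_R) for remitters seen.

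**Step 3: rates at r = q = 0.5 (true rate 25% in both arms).**

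| Loss | LOCF | All patients seen at week 16 |
|---|---|---|
| 10% in both arms, unrelated to relapse | 22.5% vs 22.5% | 25% vs 25% |
| 5% vs 15%, unrelated to relapse | 23.75% vs 21.25% | 25% vs 25% |
| 10% vs 30% of relapsers | 22.5% vs 17.5% | 0.225/0.975 = 23.1% vs 0.175/0.925 = 18.9% |

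**Step 4: false rejection over r and q of 0.3 to 0.5 (simulated, 232 per arm).**

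| Loss | LOCF | Followed-up denominator |
|---|---|---|
| None | about 5% | about 5% |
| Equal 10%, unrelated to relapse | about 5% | about 5% |
| 5% vs 15%, unrelated to relapse | about 6-10% | about 5% |
| 10% vs 30% of relapsers | about 11-27% | about 10-19% |

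The followed-up range in the last row spans both denominators, all patients seen and remitters seen.

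Hand check of the upper ends under LOCF:
- 23.75% vs 21.25%: pooled 0.225, standard error √(0.225 × 0.775 × 2/232) = 0.0388, z = 0.025/0.0388 = 0.64, rejection about 10%.
- 22.5% vs 17.5%: pooled 0.20, standard error √(0.20 × 0.80 × 2/232) = 0.0371, z = 0.05/0.0371 = 1.35, rejection about 27%.

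**Step 5: what imputation can repair.** In the relapser-loss case at r = q = 0.5, multiple imputation from arm, baseline and on-treatment scores reproduces the relapse rate among the remitters seen: 0.45/0.95 = 47.4% and 0.35/0.85 = 41.2%. Multiplied by r, that is 23.7% vs 20.6%. The false gap is 3.1 points against 5.0 under LOCF, so about 60% remains. Counting every missing remitter as recurrent restores 25% vs 25% in this case.

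**The case against.** The strongest reply is that the specific rule governs. Section 2.7.2 gives recurrence its own denominator, and a natural reading is that patients not followed up are left out. On that reading no lost patient is scored as not recurrent, and equal or unrelated loss does no harm. This stands. A reader might infer that the protocol certainly scores every lost remitter as a non-relapser. The documents do not support that, because section 2.14 does not name recurrence and section 2.7.2 can be read either way. What remains is that the two sections do not agree, and that one of the two readings gives a forced result.

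Two further inferences are tempting and also fail. The first is that the planned 10% loss produces a false difference between arms. It does not if the loss is equal: both rates fall alike and the test keeps its 5% level. The second is that the rule favours the herbal formula. The document gives no loss by arm, and the trial is double-blind and double-dummy, so the direction is unknown.

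It is fair to add that section 2.14 names only the t test and the Mann-Whitney U test, so the rejection rates describe an assumed analysis. The 10-19% on the followed-up denominator comes from informative loss and cannot be charged to LOCF. Details of imputation and sensitivity analyses are commonly left to the analysis plan. The conflict between two stated rules is not an omission of that kind.

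**Conclusion.** The point holds as a conflict between sections 2.14 and 2.7.2, with a defect on one side of it. If LOCF is applied, remitters without a week-16 score can only count as not recurrent; this follows from the definition and Table 1 alone. If only patients seen at week 16 are counted, the intent-to-treat and LOCF rule is not followed.

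The certain cost under LOCF is an understated rate, by a tenth at an equal 10% loss unrelated to relapse. A false difference between arms needs unequal loss, which is an assumption. The part due to LOCF itself is the rise from 5% to about 6-10% when loss is unrelated to relapse, and the excess of about 11-27% over 10-19% when relapsers are lost unequally. All of these figures rest on the assumed remission, relapse and loss shares and on a test that the protocol does not name.

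The outcome is secondary, and the primary IBS-SSS comparison to week 8 is untouched. The change should be made because it is cheap, but it does not threaten the main conclusion.

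**What to change.** 1. In section 2.14, state that LOCF is not applied to recurrence.
2. In section 2.7.2, define the denominator as patients in remission at week 8, so that the two sections agree.
3. Treat a missing week-16 IBS-SSS in such a patient as missing, for example by multiple imputation from arm, baseline and on-treatment scores. State that this is valid only if loss is unrelated to relapse given the observed scores.
4. Add a sensitivity analysis that counts all such patients as recurrent. This analysis has to carry the case of relapse-driven loss, since imputation leaves about 60% of the gap in the worked case. It is a bound and should not be read as an estimate.
5. Report the number of missing week-16 scores by arm.

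The cost is a few sentences and one extra analysis of data already planned for collection, with no new visits or patients. The small downside is a somewhat higher reported recurrence rate with a wider confidence interval.

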### Dropout criteria

2.5

Patients will be dropped if they are with the following conditions:

(1)With severe adverse events (AEs);(2)Unwilling to continue the study protocol.

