#### Treatment group

2.6.1

Patients in the treatment group will take Chinese herbal formula QZD, which is composed of Fengfei Cao (*Pteris multifida Poir*) 30 g, Dijin Cao (*Elsholtzia Ciliata Hyland*) 15 g, Bugu Zhi (*Psoralea corylifolia*) 15 g, Huanglian (*Coptis chinensis*) 2 g, Muxiang (*Radix Aucklandiae*) 6 g, Paojiang (*Baked ginger*) 6 g, Baishao (*Radix paeoniae alba*) 15 g, Fangfeng (*Radix Saposhnikoviae*) 10 g, Cangzhu (*Rhizoma atractylodis*) 10 g, Baizhu (*Rhizoma Atractylodis Macrocephalae*) 15 g, and Xianhe Cao (*Agrimonia pilosa*) 12 g (the ingredients of each herb are provided in Supporting Material 1). The herbs are provided as herbal concentrate-granules in 1 bag and quality controlled by Tianjiang Pharmaceutical Co., Ltd. (Jiangyin, China). Patients will orally take 100 mL of the QZD twice a day and PB-simulation 50 mg 3 times a day continuously for 8 weeks.

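### Last observation carried forward is the only stated missing-data rule, and with early, unequal dropout it can materially bias a comparison designed around 10 IBS-SSS points

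*Protocol article*

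**What the plan says.** Statistical methods (2.14) states: "Efficacy outcome parameters will be analyzed on an intent to-treat basis", and in the same sentence that "the last observation carried forward rule will be applied to manage missing data". Between-group comparison is by t test or Mann-Whitney U test. No second missing-data method appears.

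Dropout criteria (2.5) opens with "Patients will be dropped if they are with the following conditions" and lists two: severe adverse events, and "Unwilling to continue the study protocol". It does not say whether such patients are assessed afterwards.

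Primary outcome (2.7.1) takes IBS-SSS "at weeks 0, 1, 2, 4, 6, 8" and names no single primary time point. Treatment lasts 8 weeks in both arms (2.6.1, 2.6.2), so week 8 is the last on-treatment score.

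Sample size (2.10) expects falls of 115 points (QZD) and 105 points (PB), with SD 37, two-sided α of 0.05 (sidedness from 2.14) and 80% power. It asks for 212 per group and adds: "Considering a loss to follow-up of 10%, 464 cases in total will be included". That is 232 per arm.

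**The concern.** Carry-forward assumes that a patient's score stays where it was at the last visit. In this trial scores are expected to move a long way: the within-arm fall is about 110 points and the effect sought is 10, or about 9% of it. A score from week 1 or 2 can then differ from the week 8 score by several times the effect under study.

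If equal shares leave each arm at similar times, the error largely cancels from the difference, but it dilutes the effect and widens the spread. If the shares differ, the error goes straight into the treatment comparison. The two reasons for dropout in 2.5 can be related to treatment, so the shares may differ through adverse events or lack of efficacy. The direction is not known in advance: the bias works against the arm that loses more patients.

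The intent-to-treat label does not protect against this. If patients are no longer scored once dropped, every randomised patient is counted, but some week 8 values are assumed and then treated as if observed.

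**Working it through.** **The plan's own figure.** n per group = 2 × (1.96 + 0.8416)² × 37² / 10² = 214.9, so 215. The stated 212 is close (power 79.5%). With 232 per arm fully observed, SE = 37 × √(2/232) = 3.44, the smallest significant difference is 1.96 × 3.44 = 6.7 points, and power for 10 points is 83%.

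**Inputs from the protocol.** Falls of 115 and 105 (midpoint 110), SD 37, 232 per arm, 10% loss.

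**Assumptions.** The protocol gives no dropout by arm, timing or trajectory. Assume:
- dropouts have reached a fraction f of their arm's full fall when they leave;
- f is 0.125, 0.25, 0.50 or 0.75, which on a straight-line fall would correspond to weeks 1, 2, 4 and 6;
- the SD is 37 within completers and within dropouts;
- the analysis compares mean change at week 8.

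Bias is measured against the scores these patients would have had if they had continued treatment.

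**Formulas.** For an arm with fall m and dropout share d:
- mean after carry-forward = m × [1 − d(1 − f)];
- variance = 37² + d(1 − d) × [m(1 − f)]², because completers and dropouts are mixed;
- SE of the difference = √[(V₁ + V₂)/232];
- rejection probability by normal approximation, two-sided 5%.

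**No true difference (110 in both arms).** Bias = 110 × (1 − f) × difference in dropout share.

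| f | 15% v 5%: bias | SE | Type I error | 12.5% v 7.5%: bias | SE | Type I error |
|---|---|---|---|---|---|---|
| 0.125 | 9.6 | 4.33 | 60% | 4.8 | 4.35 | 20% |
| 0.25 | 8.25 | 4.12 | 52% | 4.1 | 4.13 | 17% |
| 0.50 | 5.5 | 3.75 | 31% | 2.75 | 3.76 | 11% |
| 0.75 | 2.75 | 3.52 | 12% | 1.4 | 3.52 | 7% |

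Worked row, f = 0.125, 15% v 5%: bias = 110 × 0.875 × 0.10 = 9.6. Variances are 1369 + 0.1275 × 96.25² = 2550 and 1369 + 0.0475 × 96.25² = 1809. SE = √(4359/232) = 4.33.

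**True difference of 10 points, equal 10% loss.** Estimated difference = 10 × [1 − 0.1 × (1 − f)].

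| f | Difference | SE | Power |
|---|---|---|---|
| 0.125 | 9.1 | 4.36 | 55% |
| 0.25 | 9.25 | 4.13 | 61% |
| 0.50 | 9.5 | 3.76 | 71% |
| 0.75 | 9.75 | 3.52 | 79% |

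Most of the power loss comes from the wider spread. With SE held at 3.44, a difference of 9.1 to 9.5 would still give about 76% to 79%.

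**The case against.** **Matched regimens.** A reader might infer that a decoction and a tablet will lose patients at different rates. The design does not support that. It is double-dummy: both arms take a liquid twice a day and a tablet three times a day (2.6.1, 2.6.2, 2.12). Only differences in adverse events or efficacy remain as causes, and nothing in the protocol predicts their size. This objection stands, and the 15% v 5% case illustrates a possibility; it is not a forecast.

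**The whole effect.** A reader might also infer that a modest imbalance could create or cancel all 10 points. The figures above do not show that: even 15% v 5% stays below 10. Creating 10 points from two arms that both fall by 105 needs a dropout gap of 9.5 percentage points if dropouts have not improved at all, 18.2 if they have improved by 50 points and 33 if by 75. Cancelling a true 10 points at 10% mean loss needs 14.1% v 5.9% (QZD v PB) with no improvement carried, or 17.5% v 2.5% with 50 points carried, and is impossible with 75 or more. What is supported is a material bias, enough to change significance in some scenarios.

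**Late dropout.** If most patients leave near the end, the bias is small, as the f = 0.75 rows show. That also stands.

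**Natural readings, not stated text.** The protocol does not say that scoring ends at dropout, nor that week 8 is the primary time point. Section 2.13 refers separately to patients who quit treatment. The point therefore rests partly on inference, and clarifying this is part of the fix.

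**An unseen analysis plan.** It might add sensitivity analyses. The protocol has nevertheless already fixed the rule, so this is a stated choice that can be criticised and not a missing detail.

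**Conclusion.** The concern holds in a bounded form. Carry-forward is a poor primary rule for an outcome expected to fall by about 110 points when the effect sought is 10. Under the stated assumptions, a 10-point dropout gap with early departure gives 5.5 to 9.6 spurious points and a type I error of about 31% to 60%. A 5-point gap gives 2.8 to 4.8 points and about 11% to 20%. Departure after 75% of the fall reduces these to 2.75 points (about 12%) and 1.4 points (about 7%). The power loss needs no imbalance: equal 10% loss with early departure gives about 55% to 71%, against 83% with no loss.

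Direction and size cannot be settled from the protocol. They depend on unknown dropout shares and timing, on week 8 being the endpoint, on dropped patients not being scored, and on taking continued treatment as the target. For another target the size and sign of the bias would differ, but carry-forward would still assume unchanged scores after departure. This should be fixed before data are seen; it does not by itself invalidate the trial.

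**What to change.** 1. **Statistical methods (2.14).** Replace carry-forward as the primary method by a mixed model for repeated measures on the scheduled IBS-SSS visits: baseline IBS-SSS, arm, visit and arm-by-visit interaction, unstructured covariance, treatment contrast at week 8. Keep carry-forward as a sensitivity analysis. Add a delta-adjusted analysis, because the mixed model itself assumes that data are missing at random.
2. **Dropout criteria (2.5).** State that patients who stop treatment are still scored for IBS-SSS at the remaining visits unless they withdraw consent. This concerns assessment only and leaves the rules on stopping treatment untouched. State also whether the primary model uses scores taken after treatment stopped. Using them matches the intent-to-treat claim; leaving them out targets continued treatment, which is a different question.
3. **Table 1 and Primary outcome (2.7.1).** Reconcile them: Table 1 ticks no IBS-SSS at week 0, whereas 2.7.1 lists week 0. The model needs that baseline score.

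Cost: mainly wording, since the on-treatment visits are already scheduled. The downside is some follow-up of patients who stopped treatment and a little more analysis work.

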### Participants

2.2

Participants will be recruited from inpatients in Changshu Hospital Affiliated to Nanjing University of Chinese Medicine, and they will be randomly assigned to either the treatment group and control group by a 1:1 ratio (Fig. 1).

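### The between-group test is unadjusted and chosen from the observed distribution, so the effect measure is not fixed in advance and the precision available from baseline IBS-SSS is left unused

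*Protocol article*

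**What the plan says.** **Test.** Section 2.14 makes the between-group test depend on normality and homogeneity: a group t test in one case, and in the other a Mann-Whitney U "test for non-normally distributed data will be used to compare variables between groups". No other inferential method appears in the article. "Statistical testing is 2-sided and" the threshold is 0.05. Efficacy is analysed by intention to treat, and "the last observation carried forward rule will be applied to manage missing data".

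**Outcome.** The Primary outcome section (2.7.1) has IBS-SSS record symptoms and "quality of life at weeks 0, 1, 2, 4, 6, 8, with 4 grades". A week-0 score is therefore intended, but no week is named as primary. Table 1 has no IBS-SSS tick in the week-0 column; its ticks start at week 1.

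**Sizing.** The Sample size section (2.10) states that "QZD and PB are expected to reduce the IBS-SSS by 115 points and 105 points, respectively". It continues: "Taking α = 0.05, β = 0.2, SD = 37, 212 cases will be needed in each group". Then: "Considering a loss to follow-up of 10%, 464 cases in total will be included". It does not say whether 37 is the SD of the reduction or of the final score.

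**The concern.** Two features of the stated rule can be improved.

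1. **The effect measure depends on the data.** The trial is sized on a difference in mean reduction. Under 2.14 that difference is tested only if the observed data pass distribution checks. Otherwise the test becomes Mann-Whitney, which compares ranks and does not estimate a 10-point mean difference. With more than 200 patients per arm a comparison of means is robust to moderate non-normality, while normality tests at that size tend to reject for unimportant departures. The switch therefore protects little and leaves open which quantity the trial will report.

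2. **Baseline is not adjusted for.** A test of final scores would leave any chance baseline imbalance in the estimate. A test of change scores uses baseline but, with a correlation below 1, is less precise than ANCOVA. The article does not say which of the two is meant. In both cases, precision that the week-0 measurement makes available is not used.

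**Working it through.** **Inputs from the article.** Difference 115 − 105 = 10 points; SD 37; two-sided α 0.05; power 80%; 1:1 allocation; 212 per arm; 464 in total (232 per arm); 10% loss.

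**Assumptions.** The article gives no correlation ρ between baseline and final IBS-SSS, so 0.3 to 0.7 is used, with 0.5 as the middle value. Baseline and final scores are taken to have equal variance.

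**Step 1: the plan's own figure.** n per arm = 2(z₀.₉₇₅ + z₀.₈₀)²·SD²/δ² = 2 × (1.960 + 0.842)² × 37² / 10² ≈ 215; the exact t version gives 216. The stated 212 is within 3% of this. A one-sided test would need only 170, so the calculation is two-sided and for an unadjusted comparison of two means. The stated figure is reproduced.

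**Step 2: power of the unadjusted test** (exact two-sided t test, δ = 10, SD = 37).

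- 464 less 10%: 464 × 0.9 / 2 ≈ 209 per arm, power 78.7%.
- All randomised patients analysed, as intention to treat with LOCF implies: 232 per arm, power 82.8%, provided the 10-point difference and the SD are unchanged by the carried-forward values.

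**Step 3: residual SD under ANCOVA.** If σ² is the variance of a single score, Var(change) = 2σ²(1 − ρ) and the ANCOVA residual variance is σ²(1 − ρ²).

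- If 37 is the SD of change, the variance ratio is (1 + ρ)/2 and the residual SD is 37·√((1 + ρ)/2).
- If 37 is the SD of the final score, the ratio is 1 − ρ² and the residual SD is 37·√(1 − ρ²).

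At ρ = 0.5 both ratios equal 0.75, so the residual SD is 37 × √0.75 = 32.0 under either reading.

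**Step 4: power with ANCOVA at 209 per arm**, against 78.7% unadjusted.

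| ρ (assumed) | 37 = SD of change: residual SD, power | 37 = SD of final score: residual SD, power |
|---|---|---|
| 0.3 | 29.8, 92.8% | 35.3, 82.4% |
| 0.5 | 32.0, 88.9% | 32.0, 88.9% |
| 0.7 | 34.1, 84.8% | 26.4, 97.1% |

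The smallest gain is 82.4 − 78.7 = 3.7 points and the largest is 97.1 − 78.7 = 18.4 points, so about 4 to 18. At ρ = 0.5 it is 88.9 − 78.7 = 10.2 points. At 232 per arm and ρ = 0.5, power is 91.8%, a gain of 91.8 − 82.8 = 9.0 points.

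The two readings of the SD run in opposite directions. If 37 belongs to change, a higher correlation means less to gain; if it belongs to the final score, a higher correlation means more.

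**The case against.** - **The test may already use baseline.** The sizing is in terms of reduction, so the t test may well be run on change scores. This stands. A reader might infer that the plan ignores baseline, but the article does not support that. It supports only that no covariate is named and that the analysed variable is not stated.
- **The power gain is not a document figure.** This stands too. A reader might take a gain of about 10 points as fact. It holds only near ρ = 0.5, and the article gives neither a correlation nor a definition of the SD. The range under both readings has to be shown.
- **The analysed number may exceed 209 per arm.** Intention to treat with LOCF keeps up to 232 per arm. This is accepted, and both sizes are given; the gain at ρ = 0.5 hardly changes.
- **The distribution checks are not said to be unblinded.** A reader might infer that the test is picked after seeing results by arm. Section 2.14 does not say so, and section 2.12 keeps the random number table sealed until the study is complete. The rule is also written in advance and turns on the shape of the data, not on the treatment difference. What remains is that the effect measure depends on outcome data.
- **Covariates and confidence intervals usually belong in an analysis plan.** That is fair for an omission. Here, however, the article states a specific rule that leaves the choice between two effect measures to the data, and that rule can be judged as written.

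**Conclusion.** The point holds as one of efficiency and pre-specification. A reader might conclude that the primary test is invalid or the trial underpowered, but neither follows. The unadjusted test is valid under randomisation, the stated sample size is reproduced, and power is close to plan at 78.7% to 82.8%.

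The plan does leave the reported quantity, a mean difference or a rank comparison, to the observed distribution, although the sizing rests on a mean difference. It also forgoes a gain in power of about 4 to 18 points at 209 per arm. That range rests on an assumed correlation of 0.3 to 0.7, equal variances at baseline and end of treatment, and either reading of the SD. The gain is positive in every case examined. The change should be made because it improves the trial at almost no cost.

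**What to change.** In section 2.14, make the primary analysis an ANCOVA (or equivalent mixed model) of week-8 IBS-SSS on arm and week-0 IBS-SSS. Report the adjusted mean difference with its 95% CI whatever the normality checks show, and keep the rank test as a sensitivity analysis. Use the same model for the secondary scales that have a baseline, each with its own baseline as covariate.

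Two points must be settled with it:

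- Section 2.7.1 names no primary time point. State week 8, the end of treatment, explicitly.
- Table 1 shows no week-0 IBS-SSS assessment while section 2.7.1 lists one. Reconcile them so that the baseline score is collected before treatment.

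It would also help to say in section 2.10 whether 37 is the SD of the change or of the final score.

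The cost is wording. No further patients are needed, nor any visit beyond the week-0 enrolment visit already in Table 1, and SPSS, the named software, fits the model.
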